#### Follow-up visit

Seven days after treatment visit, participants will be followed up. The degree of joint pain, swelling, redness, and mobility will be scored, and the adverse events during this 7-day period will be recorded. The medications and treatment received during the follow-up period will also be recorded.

### Participants and recruitment

#### Recruitment and informed consent

Participants will be recruited from the outpatient department of the listed three hospitals. For all patients who come to the hospital for AGA and are likely to meet the eligibility criteria, investigators will introduce the entire study and informed consent to them, mainly including the study process and intervention methods. Patients will be informed that their participation in this study is entirely voluntary and they are free to withdraw from the study at any time. After signing informed consent and assessed for eligibility criteria, eligible patients will be invited to participate in the study.

#### Inclusion criteria

Patients will be eligible for this study if they fulfill the following inclusion criteria:Meeting the ACR (American College of Rheumatology)/EULAR (European League Against Rheumatism) gout classification criteria [27]Joint pain intensity score (visual analogue scale, VAS, 0–10 points) ≥3 pointsWith an acute flare of gout, the time from the onset to the visit to hospital should not exceed 1 weekAged between 18 to 65 years oldVolunteer to participate in the study and sign the informed consent

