### Study process

#### Baseline visit

After signing an informed consent, patients will be interviewed to obtain information on demographic characteristics, history of past and present illness, and current medications. General physical examination (including height, weight, blood pressure, respiratory rate, heart rate, and temperature) and laboratory tests (including serum uric acid and C-reactive protein) will be conducted. Degree of joint pain, swelling, redness, and mobility will be scored, and width and thickness of affected joints will be measured. Patients who meet the eligibility criteria will be randomly assigned to treatment group and control group, with 103 patients in each group. Investigators will also instruct participants on how to score the degree of joint pain, swelling, redness and mobility, and how to measure the width and thickness of joints.

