### Assignment of interventions

#### Randomization

Participants will be randomly assigned to treatment group and control group at a ratio of 1:1, with 103 cases in each group. The random sequence was generated by an independent statistician, using the SAS 9.2 software.

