#### Allocation concealment and blinding

Sequentially numbered drug containers of identical appearance were used to achieve allocation concealment. Two hundred and six drug boxes with identical appearance were numbered as 001–206. According to the random sequence, Qingpeng ointment and placebo ointment were put into the corresponding numbered boxes, with three tubes of Qingpeng ointment or placebo ointment in each box. One box of DSSRT was also put into each drug box at the same time. Special personnel are assigned to manage the study drugs in each hospital, and the corresponding sequence of drugs will be distributed to each patient according to their recruitment sequence. Throughout the study, the investigators and the participants will not know which group the participants are assigned to. For each participant sequence, a corresponding emergency letter was made, which records the allocation result of that participant. When a participant experience serious adverse events and the allocation result needs to be known, investigators can open the emergency letter. The process of unblinding, including reasons, time, and treatment results, should be recorded on the case report form.

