### Outcomes

#### Primary outcomes

Because the objective of this study is to investigate the efficacy of Qingpeng ointment for relieving pain and swelling of joints in patients with AGA, changes in joint pain severity (measured using VAS), joint swelling degree (measured using VAS), and width and thickness of affected joints (measured using vernier calipers) between baseline and treatment completion will be considered as the primary outcomes.Joint pain: Degree of joint pain will be measured by participants, using a visual analogue scale (VAS, 0–10 points, 0=no pain, 10=intolerable pain), at baseline, every day during treatment, and after 7-day treatment.Joint swelling:2.1 The width and thickness of each affected joint will be measured using vernier calipers (brand: Ruineng, model: NR0139) at baseline, every day during treatment, and after 7-day treatment.2.2 Degree of joint swelling will be measured by participants, using a visual analogue scale (VAS, 0–10 points, 0=no swelling, 10=intolerable swelling), at baseline, every day during treatment, and after 7-day treatment.

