### Sample size estimation

This study includes two primary outcomes: joint pain and joint swelling. Sample size was estimated based on these two primary outcome measures. Estimation according to joint pain was based on results from a previous study [23]. In this study, 47% participants in treatment group (Qingpeng ointment plus diclofenac sodium tablets) had significant relief of joint pain (the score of joint pain degree measured by a self-developed scale reduced by 6 points), and 25% participants in control group (diclofenac sodium tablets) had significant relief of joint pain. On the basis of a 5% type I error rate (*α*=0.05) and a power of 90% (*β*=0.1), the sample size of each group was 82. Assuming a 20% dropout rate, a total of 206 participants should be recruited, with 103 participants in each group.

Estimation according to joint swelling was likewise based on results from another previous study [19], which established score of joint swelling measured by a 0–3 points scale as 0.45 points after receiving Qingpeng ointment plus etoricoxib tablets, and the estimated standard deviation is 0.37. Score of joint swelling after receiving vaseline plus etoricoxib tablets is 0.87, and the estimated standard deviation is 0.64. On the basis of a 5% type I error rate (*α*=0.05) and a power of 90% (*β*=0.1), the sample size of each group was 27. Assuming a 20% dropout rate, a total of 68 participants should be recruited, with 34 participants in each group.

Based on these results, we chose the larger sample size of 206 participants, with 103 participants in each group.

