### Statistical analysis

Statistical analysis will be performed using SAS 9.2 software, with a statistical significance of *p* value less than 0.05. Normally distributed continuous variables will be described using mean ± standard deviation (SD), and non-normally distributed continuous variables will be described using median and interquartile range (IQR). Categorical variables will be described using frequencies and percentages. Primary outcomes will be analyzed according to the intention-to-treat principle. Intra-group differences of continuous variables will be tested for significance using paired-samples *t* test when the data is normally distributed, and will be tested using non-parametric test when the data is non-normally distributed. Between-group differences of continuous variables will be tested for significance using independent-samples *t* test when the data of the two groups are normally distributed and have equal variance, and will be tested using non-parametric test when the data of the two groups are non-normally distributed or have unequal variances. Chi-square test will be used for categorical data. Data from participants who drop out from this study will be implemented by the last-observation-carried-forward (LOCF) method. Interim analyses will not be performed. For the co-primary endpoints, Bonferroni correction will be performed to correct multiplicity.

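### The primary comparison of 7-day change uses neither the baseline score nor days since flare onset, both known before randomisation, and so gives up some precision (minor)

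*Protocol article*

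**What the plan says.** **Entry.** Under Inclusion criteria, patients need a pain VAS of at least 3, and "the time from the onset to the visit to hospital should not exceed" one week. A site cannot confirm eligibility without establishing when the flare began. The Baseline visit section has staff take the "history of past and present illness" and record the pain and swelling scores and joint dimensions before allocation.

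**Outcome.** Under Primary outcomes, changes in pain VAS, swelling VAS, and joint width and thickness "between baseline and treatment completion will be considered as the primary outcomes". Treatment lasts 7 days, so the entry window is as long as the period over which change is measured.

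**Analysis.** The Statistical analysis section states: "Between-group differences of continuous variables will be tested for significance using independent-samples" t test if the data are normal with equal variance. Otherwise they "will be tested using non-parametric test when the data of the two groups are non-normally distributed or have unequal variances". No covariate is named for either route.

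**Allocation.** The Randomization section says "Participants will be randomly assigned to treatment group and control group at a ratio of 1:1, with 103 cases in each group". Under Allocation concealment and blinding, "the corresponding sequence of drugs will be distributed to each patient according to their recruitment sequence". No stratification factor is named, so flare stage is not balanced by design either.

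**The concern.** Two patients who both score 5 on the pain scale, one on day 1 of a flare and one on day 6, need not have the same expected change over the next week. Nor need two patients who enter on the same day with scores of 4 and 9. Both facts are known before randomisation. A test that ignores them leaves their contribution in the error term, so the interval for the treatment difference is wider than it has to be.

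The protocol names the test, so this is a stated method and not a detail left to an analysis plan. What is at stake is precision on the pain and swelling outcomes. Adding covariates after the data have been seen would be post hoc, so the choice has to be made beforehand.

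**Working it through.** **1. The plan's own figure.** Sample size estimation gives 82 per group for pain, from 47% against 25%, "On the basis of a 5% type I error rate" and 90% power. With the average proportion 0.36 and one-sided alpha: 2 × 0.36 × 0.64 × (1.645 + 1.282)² / 0.22² = 81.5, so 82. With 20% dropout, 82 / 0.80 = 102.5, so 103 per group and 206 in all. The figure reproduces only with one-sided alpha; at two-sided 0.05 the same formula gives 100.04, and 82 per group has 84.2% power. This calculation is for a binary responder outcome. It contains no SD for VAS change and no correlation of any covariate with that change, so the gain cannot be computed from the documents.

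**2. Formula.** If covariates explain a share R² of the outcome variance, the standard error of the treatment difference is multiplied by √(1 − R²). The share that onset adds beyond baseline is (R² with both − R² with baseline) / (1 − R² with baseline).

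**3. Assumed flare courses.** All of these inputs are assumptions:
- entry uniform over 0 to 7 days, with pain VAS at least 3 at entry
- peak pain with mean 8 and SD 1.3
- exponential decay, or a 2-day plateau followed by decay
- pain half-life 4 or 7 days
- log-SD of the decay rate between patients 0, 0.3 or 0.6
- measurement SD 0.5 or 1.0

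That makes 2 × 2 × 3 × 2 = 24 scenarios. Pain change was regressed on onset, on baseline, and on both:

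| Explained | Range over 24 scenarios |
|---|---|
| Baseline score alone | 15% to 83% |
| Onset alone | about 3% to 50% |
| Onset, as a share of what baseline leaves | 0% to 19%, median about 2.6%; below 6% in 18 of 24 |

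Two scenarios, both with exponential decay, half-life 4 days and measurement SD 0.5:
- Decay rate equal for all patients: baseline 0.833, both 0.836. Onset adds (0.836 − 0.833) / (1 − 0.833), about 2%.
- Decay-rate log-SD 0.6: baseline 0.340, both 0.464. Onset adds (0.464 − 0.340) / (1 − 0.340), about 19%. This is the largest gain.

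Baseline alone supplied at least about 60% of what the two covariates explained together. The lowest case was 0.149 / 0.247 = 0.60.

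**4. Effect on the standard error.**
- Baseline: √(1 − 0.15) = 0.92, a reduction of about 8%; √(1 − 0.83) = 0.41, a reduction of about 59%.
- Onset, in addition: √(1 − 0.026) = 0.987, about 1.3%; √(1 − 0.19) = 0.90, 10%.

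**5. Illustrative power.** Suppose the baseline-adjusted test had 84.2% power, with noncentrality 1.960 + 1.002 = 2.962. Adding onset at the median share gives 2.962 / 0.987 = 3.001, or about 85%. At the 19% extreme it gives 2.962 / 0.90 = 3.291, or about 91%. The 84.2% is borrowed from the responder calculation in step 1 and does not describe the VAS test.

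**6. Validity.** In 10,000 simulated trials with 82 per arm and two-sided 0.05, type I error without and with adjustment was 0.051 and 0.050 for a covariate–outcome correlation of 0.3, and 0.052 and 0.053 for 0.5. Both analyses hold their level.

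**The case against.** The strongest reply is that nothing here is an error. An unadjusted test in a randomised trial is unbiased and keeps its type I error, as step 6 shows. No passage calls the flare self-limiting, describes its course or links onset time to outcome. That stands, and it is why the point is minor.

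A reader might infer that a chance difference in flare age between arms would be mistaken for a drug effect. With onset uniform over 0 to 7 days its SD is 7/√12 = 2.02 days. The 95% range for the difference in means with 103 per arm is then 1.96 × 2.02 × √(2/103) = ±0.55 days. Such a difference can move one trial's estimate, but the standard error of the unadjusted test already allows for it. It is not bias.

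A reader might also take the 3% to 50% explained by onset alone as the gain on offer. Most of that overlaps with the baseline score, and only the remainder belongs to onset.

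The assumed courses can be challenged too. They have no rising phase; runs that added one gave onset about 3% to 48% of what baseline leaves, depending on the curve. They also omit rescue diclofenac and last-observation-carried-forward, and they simulate pain only, not swelling VAS or joint width and thickness. This means that the size is unknown, not that it is zero.

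Finally, a covariate does not drop into the non-parametric fallback, so the change replaces the testing framework. That is a real cost and is counted under the fix.

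What survives is narrow: two pre-randomisation values are in hand, the named test uses neither, and prespecifying them costs little.

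**Conclusion.** The point holds as a low-cost improvement of minor severity. The planned comparison is valid but less precise than the collected data allow. Under the assumed courses most of the recoverable precision comes from the baseline score (15% to 83% of the variance of pain change). Days since onset adds 0% to 19% of the remainder, median about 2.6%, which is roughly 84% to 85% power on the borrowed reference. Its own contribution may be negligible, though it could be larger if many patients enter while pain is still rising.

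These figures rest on assumed entry times, curves and measurement error, and for swelling and joint dimensions no figure is available. The documents do not support a claim that the trial's conclusion would be biased, or that the one-week entry window is wrong.

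**What to change.** Before unblinding, amend the Statistical analysis section so that the primary between-group analysis of each change (pain VAS, swelling VAS, joint width and thickness) is a linear model with treatment, the baseline value of that outcome and days from onset to randomisation as prespecified covariates. Report the adjusted difference with its confidence interval, and apply the planned Bonferroni correction to these tests. Keep a rank-based or unadjusted test as a sensitivity analysis. Record days from onset on the case report form, taking the value from the eligibility check.

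Cost: two degrees of freedom, leaving 206 − 4 = 202 for error instead of 204 with complete data, and one field on the form. The model also replaces the present choice of test by normality and equality of variance. The entry window, visits and sample size do not change.

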#### Exclusion criteria

Patients will not be enrolled into this study if they meet the following exclusion criteria:Also suffering from other types of arthritisAllergic to the study drugs (Qingpeng Ointment, DSSRT)With severe cardiovascular, cerebrovascular, liver, or kidney diseasesWith mental diseases or senile dementiaWomen during pregnancy and lactationWith skin ulceration at the affected joint(s)Having newly added uric acid-lowering drugs for any reason in the past weekParticipating in other clinical trials at the same time

#### Withdrawal or dropout criteria

Participants will withdraw from this study in the following cases:Deciding to withdraw by themselvesNo longer continuing to use the study drugs or accept visitsHaving severe allergic reaction at the administration siteExperiencing serious adverse events or complications

### Interventions

#### Experimental group

Participants in treatment group will be treated with Qingpeng ointment (produced by Tibet Cheezheng Tibetan Medicine Co., Ltd; specification: 20g/ointment aluminum tube). The ingredients of Qingpeng ointment are given in Table 1. Every participant will be given three tubes of ointment. Participants should first clean the skin of affected joints and then apply the ointment to the skin. The dosage is that the ointment can cover the surface of affected joints, and the thickness is 0.3–0.5 cm. The applied part needs to be massaged gently until the ointment is totally absorbed by the skin. The duration of each application is approximately 0.5 h, the frequency of application is twice a day, and the interval between two applications is at least 8 h. The course of treatment is 7 days.

**Table 1 Tab1:** Ingredients of Qingpeng ointment

Ingredient	Dose (g)
*Herba Oxytropis Falcatae* (Jidou)	100
*Rhei Spiciforme Randix* (Yadahuang)	50
*Radix Aconiti Flavi Et Penduli* (Tiebangchui)	75
*Chebulae Fructus* (Hezi)	100
*Terminaliae Belliricae Fructus* (Maohezi)	100
*Phyllanthi Fructus* (Yuganzi)	100
*Benzoinum* (Anxixiang)	35
*Caulis Tinosporae* (Kuanjinteng)	150
*Moschus* (Shexiang)	25

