#### Placebo group

In order to evaluate the absolute efficacy and safety of Qingpeng ointment for AGA and reduce the risk of bias, we chose placebo as comparison. Participants in control group will be treated with placebo ointment (produced by Tibet Cheezheng Tibetan Medicine Co., Ltd). The ingredients of placebo ointment include purified water, liquid paraffin, glycerinum, methylparaben, and food coloring. The placebo ointment is the same as Qingpeng ointment in texture, color, smell, and packaging. The usage of placebo ointment is the same as Qingpeng ointment.

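### The stated 0.3–0.5 cm layer can be supplied from the packed 60 g only up to a total treated area of about 9–14 cm² (assumed density 1.0 g/cm³), so dose and supply need to be made to agree

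*Protocol article*

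**What the plan says.** All the dosing facts are in the protocol article, under Interventions and Allocation concealment and blinding.

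- **Layer and area** (Experimental group): "The dosage is that the ointment can cover the surface of affected joints, and the thickness is 0.3–0.5 cm". No dose in grams and no treated area is given.
- **Supply** (Experimental group): "Every participant will be given three tubes of ointment", with "specification: 20g/ointment aluminum tube". Allocation concealment and blinding repeats this for the numbered boxes: "with three tubes of Qingpeng ointment or placebo ointment in each box". No resupply is described.
- **Schedule** (Experimental group): "The duration of each application is approximately 0.5 h, the frequency of application is twice a day". The course is 7 days.
- **Manner of application** (Experimental group): "The applied part needs to be massaged gently until the ointment is totally absorbed by the skin".
- **Placebo** (Placebo group): "The usage of placebo ointment is the same as Qingpeng ointment".
- **Joints treated**: the inclusion and exclusion criteria limit neither the number nor the size of affected joints. Primary outcomes expects that there may be more than one: "The width and thickness of each affected joint will be measured using vernier calipers".
- **Leftover ointment**: Treatment visit has it returned and recorded. The Discussion uses the remaining amount to judge compliance.

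**The concern.** Layer thickness is the only statement of how much ointment goes on a given area of skin. Together with the schedule and the fixed supply, it implies a ceiling on the area that can be treated. That ceiling is small, and nothing in the eligibility criteria keeps participants below it.

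Three things are at stake. First, a participant above the ceiling who follows the text literally would use up the ointment before the end of treatment, when the primary outcomes are assessed, and so would not receive the stated 7-day regimen. Second, a reader or later user could not tell which dose to reproduce, the layer or the packed amount. Third, the compliance check becomes hard to read: an empty box at day 7 could mean full adherence or a supply that ran out days earlier.

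**Working it through.** The document states no total consumption and no treated area, so there is no figure of its own to reproduce. The check is supply arithmetic.

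**Inputs from the protocol article**
- 3 tubes of 20 g (Experimental group; three tubes per box confirmed under Allocation concealment and blinding)
- 2 applications a day for 7 days (Experimental group)
- Layer t = 0.3–0.5 cm (Experimental group)

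**Assumptions, not in the document**
- Ointment density ρ = 1.0 g/cm³, with 0.85–1.2 shown as a range
- Treated areas of 5–25 cm², for illustration only

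**Step 1. Amount per application**

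3 × 20 g = 60 g; 2 × 7 = 14 applications; 60 / 14 = 4.29 g.

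**Step 2. Largest total area that the supply covers for the full course**

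Area = 4.29 / (ρ × t)

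| Density (g/cm³) | t = 0.3 cm | t = 0.5 cm |
|---|---|---|
| 0.85 | 16.8 cm² | 10.1 cm² |
| 1.0 | 14.3 cm² | 8.6 cm² |
| 1.2 | 11.9 cm² | 7.1 cm² |

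At density 1.0 this equals one square patch of √8.6 = 2.9 cm to √14.3 = 3.8 cm a side, for all joints together.

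**Step 3. Need for assumed areas, density 1.0**

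Course need = area × t × 14; full applications available = 60 / (area × t).

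| Assumed area | Need at 0.3 cm | Need at 0.5 cm | Result |
|---|---|---|---|
| 5 cm² | 21 g | 35 g | Enough throughout |
| 10 cm² | 42 g | 70 g | Enough up to 4.29 / 10 = 0.43 cm; at 0.5 cm, 60 / 5.0 = 12 applications (end of day 6) |
| 15 cm² | 63 g | 105 g | 3–45 g short; 60 / 4.5 = 13.3 down to 60 / 7.5 = 8 applications |
| 25 cm² | 105 g | 175 g | 60 / 7.5 = 8 applications (end of day 4) down to 60 / 12.5 = 4.8 (day 3) |

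**Step 4. What if the unit were millimetres?**

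At 0.03–0.05 cm and density 1.0: 4.29 / 0.03 = 143 cm² and 4.29 / 0.05 = 86 cm² per application. That sits far more easily with the packed supply.

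**Step 5. Consistency within the section**

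The layer is to be massaged in until fully absorbed, and each application lasts about half an hour. Whatever the area, 3–5 mm of ointment is hard to reconcile with that; a layer one tenth as thick is not. This points to a slip in the unit but does not prove it.

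**The case against.** The strongest reply is that layer and supply conflict only above a threshold, and the document gives no treated area. At 5 cm² the supply is ample, at 10 cm² it lasts for most of the stated layer range, and at 15 cm² and 0.3 cm it falls only 3 g short. The large shortfalls need larger assumed areas. This stands. A reader might infer that layer and supply contradict each other for every participant, or that participants did run out. The document supports neither: both depend on an unstated area and on sites having taught a literal 3–5 mm. Nor can everyone below about 9 cm² be called safe, because at density 1.2 and 0.5 cm the limit is 7.1 cm².

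A second reply is that the internal evidence favours a typing slip. The ointment is to be fully absorbed, and leftovers are expected and recorded. If so, nobody is under-dosed and one unit needs correcting. That is plausible, but it leaves the printed figure wrong, and the document cannot settle which figure is at fault. A reader who takes the slip as established goes further than the text allows.

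A third reply is that inference is barely touched. Usage is the same in both arms, and randomisation, blinding and the intention-to-treat comparison are unaffected. This also stands: a reader might suspect between-arm bias, and there is no ground for it. What remains is possible under-delivery of unknown extent and a dose that cannot be reproduced.

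Finally, an article may condense practical dosing instructions. But this point does not rest on a missing detail. The layer, the schedule and the supply are all stated, and they agree only for small areas.

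**Conclusion.** The point holds in conditional form. As written, the layer can be delivered for the full 7 days only if the total treated area is at most 8.6–14.3 cm² at density 1.0, or about 7–17 cm² over densities 0.85–1.2. Above that, a participant who applies the stated layer literally exhausts the supply before the day-7 assessment. The share of participants affected cannot be computed, because joint areas are not given.

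The conclusion rests on the assumed density, which does not change it over the range shown, on a literal reading of the layer, and on no resupply, which the three tubes per numbered box make a reasonable reading. The consequence is a possible shortfall equal in kind in both arms, a dose that others cannot reproduce, and a compliance measure that is hard to interpret. It is worth correcting because the figure is wrong or unworkable as printed and checking it is cheap.

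**What to change.** Make layer and supply agree.

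1. Check the thickness against the full protocol and the product label.
2. If it is a unit slip, correct it to 0.3–0.5 mm; 60 g then covers about 86–143 cm² per application.
3. If it is not, replace the thickness with the amount that the supply can deliver: about 4.3 g per application in total over all treated joints.
4. In either case keep the packed boxes and the 7-day course. Report grams used, from the ointment returned at the treatment visit, by number and site of treated joints. Do not treat an empty supply as proof of full compliance.

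**Cost.** If only the article is wrong, this is a wording correction. If sites taught 0.3–0.5 cm, it is a documented amendment: the Ethics section calls for approval by each centre's ethics committee and a revision at the registry, sites need re-instruction, and participants before and after would be on different layers. Trial status describes recruitment as active but expected it to end in December 2021. If recruitment is finished or nearly so, correcting the text and reporting grams used is the proportionate step. The 206 boxes and the blinding do not change.
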